### 4) Radiographic evaluation

Besides adjacent disc degeneration (primary outcome measure), we will also evaluate the cervical curvature, segmental motion, displacement or migration of the implant, and heterotopic ossification using the classification of McAfee[38].

### Sample size

The sample size calculation is based on the hypothesis that the incidence of symptomatic adjacent disc disease after cervical disc prosthesis is equal to anterior discectomy with or without interbody fusion. Based on the literature, the annual incidence of symptomatic adjacent disc disease after ACDF and ACDP is 7% and 0.65% respectively[18]. However, in that trial only 74 patients underwent disc arthroplasty and the probability of adjacent disc degeneration may be higher. Therefore, in our study, we assume an annual incidence of adjacent disc degeneration of 2% after arthroplasty and 7% after interbody fusion for the power calculations. We require a power of 90%, a significance level of 0.05, and assume committed accrual duration of 3 years. We plan a group sequential design with 2 interim analyses using a survival model approach for "time-to-degeneration" and a test-for-superiority approach. The East software (version 5) is used for the design of this study. The assumptions (2% vs. 7% to be detected) correspond to a Hazard Ratio of 0.28. With an accrual of 150 patients per year during 3 years, the required power is attained for a two-group comparison. Since we intend to perform two 2-group comparisons separately, we need 1.5*450 = 675 patients in total. Assuming a loss to follow-up of 10%, a total of 750 patients are needed. The interim analyses are performed only for the main comparison of ACDF versus ACDP. Stopping is allowed for futility as well as efficacy and follows prespecified alpha and beta spending rules.

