## Methods/Design

We designed an observer and patient blinded randomised cost-effectiveness trial in the treatment of cervical disc herniation in which three surgical techniques are compared in a parallel group design. Adjacent level disease will be used as primary outcome measure and NDI as secondary outcome. As such we will evaluate the clinical appropriateness and superiority of disc prosthesis on one hand, cervical fusion on the other hand, and compare this to discectomy without any implant. The follow-up period will last 5 years.

In order to collect enough patients, a multicenter design is necessary. The clinical centers that are planned to recruit patients into the NECK trial are: Medical Center Haaglanden, The Hague; Leiden University Medical Center; University Medical Center Groningen; Medical Center Alkmaar; and University Medical Center Maastricht. The protocol was approved by the ethics committee/IRB in each participating hospital.

The primary question of the NECK trial is whether ACDP has a lower incidence of symptomatic adjacent disc degeneration compared to ACD and ACDF. Symptomatic adjacent level disease is defined as development of new symptoms (i.e. neck pain, radiculopathy, or myelopathy) referable to a motion segment adjacent to the site of the previous anterior surgery. In addition, we want to identify certain subgroups that may benefit more of one of the allocated treatments.

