### Data Analysis

The data will be analysed according to the stopping rules, i.e. after approximately 1.8, 2.6 and 3.2 years under H0 and 2.2, 3.2 and 4.2 years under H1. The actual analysis times depend on the number of events observed (15, 30 and 45). This establishes an answer to the main objectives in terms of the comparison of ADCF to ADCP. Long-term analyses of all results will be conducted irrespective of an early achievement of futility or efficacy establishing a comparison at 52, 104, 156, 208 and 260 weeks. However, these analyses will be performed after the final analysis of the trial has reached the conclusion of efficacy or futility. For all analyses, assessments performed at the first outpatient visit will be taken as baseline. Baseline comparability will be analysed by descriptive statistics to determine whether randomisation was successful. Baseline measurements will be used as covariates in the analyses to increase power. Differences in outcome measures between the 2 pairs of groups, together with 95% confidence intervals, will be calculated. All data are analysed according the "intent-to-treat principle".

The primary research objective will be tested using two likelihood ratio tests for the hazard ratio's, one for the comparison to ACD and one to ACDF. In case of homogeneity of effects, a pooled effect (adjusting for interbody fusion) will be reported. Otherwise the two analyses will be reported separately. The secondary outcome continuous measures will be compared using two t-tests in the same way (or non-parametric counterparts in case of non-symmetrical or distributions with outliers), possibly after transformations of skewed distributions.

On the other hand, repeated measurements analyses of variance for the secondary outcome measures (the continuous outcome scales) will also be performed in order to compare the evolving patterns over time.

In addition, an explorative subgroup analysis is conducted to investigate whether the treatment effect varies over specific subgroups of patients (Table 4).

**Table 4 T4:** Selected prognostic variables for subgroup analysis.

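### The primary objective rests on two tests that share the ACDP arm, each at an unsplit 0.05 with no testing order, so the chance of at least one false rejection is about 9%, not 5%

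*Protocol article*

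**What the plan says.** The Methods/Design section sets one primary question with two comparators: "The primary question of the NECK trial is whether ACDP has a lower incidence of symptomatic adjacent disc degeneration compared to ACD and ACDF". The Data Analysis section tests the primary objective with "two likelihood ratio tests for the hazard ratio's, one for the comparison to ACD and one to ACDF". It adds that a pooled effect is reported if the two effects are homogeneous, and that the two analyses are otherwise reported separately.

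The Sample size section gives one error rate: "We require a power of 90%, a significance level of 0.05". The 450 patients derived from it are for a single two-group comparison. The step to three arms is "Since we intend to perform two 2-group comparisons separately, we need 1.5*450 = 675 patients in total", which becomes 750 after allowance for 10% loss to follow-up.

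On the sequential plan, the same section says "The interim analyses are performed only for the main comparison of ACDF versus ACDP". The Data Analysis section gives looks at 15, 30 and 45 events, which serve that comparison.

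**The concern.** Two tests stand under one primary objective, and either could be reported as a finding about the prosthesis. The factor 1.5 pays for the third arm's patients; it does nothing to the significance level. Each comparison therefore appears to keep the full 0.05. Nothing says that one test must succeed before the other is read, or that both must succeed.

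Both tests use the same ACDP arm. A chance run of few events in that arm pushes both towards a false claim for the device. The stated 0.05 would then understate the risk that the trial wrongly reports a difference on its primary objective.

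**Working it through.** **Reproducing the plan's figures.**
- Hazard ratio: ln(0.98)/ln(0.93) = 0.278, stated as 0.28.
- Total: 1.5 × 450 = 675; 675/0.90 = 750. Both agree.
- The 1.5 takes two arms of 225 to three arms of 225 and carries no adjustment of the significance level.

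**Inputs.**
- Level 0.05 per comparison (Sample size). That the second test uses the same level follows from the scaling by 1.5; the article does not say so in words.
- Equal allocation (Randomisation procedure).
- Sidedness is not stated. The tests are likelihood ratio tests, and of the intervals the plan says "Differences in outcome measures between the 2 pairs of groups, together with 95% confidence intervals, will be calculated", which suggests two-sided. The question about a lower incidence would allow one-sided. Both are computed.
- Null case: all three arms have the same event rate. This is also the hypothesis with which the Sample size section opens.

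**Correlation.** Each statistic is a difference between one comparator and ACDP. With equal arms, each arm contributes variance v, each difference has variance 2v, and their covariance is v. So rho = v/2v = 0.5.

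**Chance of at least one false rejection** = p1 + p2 − P(both), from the bivariate normal with rho = 0.5.

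| Reading | p1 + p2 | P(both) | At least one |
|---|---|---|---|
| Two-sided 0.05 each, any rejection | 0.10 | 0.0093 | 0.0907 |
| Two-sided 0.05 each, only claims favouring ACDP | 0.05 | 0.0046 | 0.0454 |
| One-sided 0.05 each | 0.10 | 0.0122 | 0.0878 |

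For reference, two independent tests would give 1 − 0.95² = 0.0975.

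**Does the sequential plan matter?** The spending functions are not given, so two common types were assumed. The ACDF test was simulated in 2,000,000 null trials with three equally spaced looks, and the ACD test was done once at its full level.
- Two-sided: 9.1% (O'Brien-Fleming type) and 9.3% (Pocock type), against 9.07% without looks.
- Two-sided tests, claims favouring ACDP only: 4.5% and 4.6%.
- One-sided 0.05: 8.8% and 9.0%.

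The looks add almost nothing, because alpha spending holds the ACDF test at its own level.

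**The case against.** **The plan already ranks the comparisons.** It calls ACDF versus ACDP the main one, gives only that one stopping rules, and says the sequential analyses answer the main objectives in terms of it. This is the strongest counter-argument. It shows a priority, but not a testing order: the Data Analysis section still puts both tests under the primary objective and allows separate reporting.

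**The plan never promises 5% across both tests, and its question can be read as requiring both.** If both had to succeed, no adjustment would be needed. But the article states no such rule. The null hypothesis in the Sample size section covers discectomy with and without fusion together, so 5% for that hypothesis is the natural expectation.

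**Detail on multiplicity is often left to the SAP.** That is fair, and an order may be set there. The point here is narrower: the article itself fixes one unsplit level, two separate primary tests and a sample size built on them.

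**Stronger readings a reader might infer, which the documents do not support.**
- That the error arises because only one comparison is in the sequential plan. The working shows it does not.
- That the ACD test would be read with too few events if the ACDF comparison stops early. No such reading time is prescribed; analyses of all results continue to 260 weeks regardless of early stopping.
- That the pooled effect is a third test. The article says only that it is reported.
- That joint power for beating both comparators falls to a particular figure below 90%. The two statistics' correlation under the alternative differs from 0.5, and the article makes no joint claim.

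**Conclusion.** The concern holds for the two unadjusted tests. With two-sided tests, the chance of at least one false rejection on the primary objective is about 9.1%. In favour of the prosthesis it is 4.5% where 2.5% is nominal. With one-sided tests at 0.05 it is 8.8%. On each reading this is nearly double the single-test level.

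The figures assume equal arms, no true difference between any of the three treatments, and 0.05 for each comparison. The assumed spending functions shift them by about 0.2 percentage points at most. The 90% can be taken only as the power of a single two-group comparison.

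**What to change.** Turn the main-comparison label into a fixed sequence:
1. Test ACDP versus ACDF first, within the group-sequential boundaries.
2. Only if that is significant, test ACDP versus ACD once, at 0.05, at one prespecified time, for example the planned 260-week analysis.
3. Otherwise report ACDP versus ACD as an estimate with a confidence interval.
4. State that the pooled effect is descriptive.
5. State that 90% is the power of the ACDP versus ACDF test only.
6. State whether the tests are one-sided or two-sided.

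The second test should be tied to a calendar time, not to the 45 events of the ACDF design. If ACD also ran at 2% a year, two arms of 225 followed for five years would yield about 450 × (1 − 0.98⁵) = 43 events, so a 45-event trigger might never be reached.

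The cost is wording and no extra patients. The downside is that the ACD comparison is not confirmatory if the first test fails. If the sponsor cannot accept that, splitting the level at 0.025 each also keeps the total at or below 5%. At a hazard ratio of 0.28 this raises the fixed-design two-sided requirement from 26 to 31 events (Schoenfeld) and lowers power at 45 events from 99.0% to 97.9%. Those power figures ignore the sequential looks and futility stopping.

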### Data Analysis

The data will be analysed according to the stopping rules, i.e. after approximately 1.8, 2.6 and 3.2 years under H0 and 2.2, 3.2 and 4.2 years under H1. The actual analysis times depend on the number of events observed (15, 30 and 45). This establishes an answer to the main objectives in terms of the comparison of ADCF to ADCP. Long-term analyses of all results will be conducted irrespective of an early achievement of futility or efficacy establishing a comparison at 52, 104, 156, 208 and 260 weeks. However, these analyses will be performed after the final analysis of the trial has reached the conclusion of efficacy or futility. For all analyses, assessments performed at the first outpatient visit will be taken as baseline. Baseline comparability will be analysed by descriptive statistics to determine whether randomisation was successful. Baseline measurements will be used as covariates in the analyses to increase power. Differences in outcome measures between the 2 pairs of groups, together with 95% confidence intervals, will be calculated. All data are analysed according the "intent-to-treat principle".

The primary research objective will be tested using two likelihood ratio tests for the hazard ratio's, one for the comparison to ACD and one to ACDF. In case of homogeneity of effects, a pooled effect (adjusting for interbody fusion) will be reported. Otherwise the two analyses will be reported separately. The secondary outcome continuous measures will be compared using two t-tests in the same way (or non-parametric counterparts in case of non-symmetrical or distributions with outliers), possibly after transformations of skewed distributions.

On the other hand, repeated measurements analyses of variance for the secondary outcome measures (the continuous outcome scales) will also be performed in order to compare the evolving patterns over time.

In addition, an explorative subgroup analysis is conducted to investigate whether the treatment effect varies over specific subgroups of patients (Table 4).

**Table 4 T4:** Selected prognostic variables for subgroup analysis.

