**Discussion:**

Currently, anterior cervical discectomy with fusion is the golden standard in the surgical treatment of cervical disc herniation. Whether additional interbody fusion or disc prothesis is necessary and cost-effective will be determined by this trial.

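### Separate hazard ratios are promised only if effects differ, and ACDF versus ACD, a stated aim, has no named contrast

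*Protocol article*

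**What the plan says.** The Data Analysis section plans two likelihood ratio tests for the primary event, one of ACDP against ACD and one of ACDP against ACDF. It then sets a reporting rule: "In case of homogeneity of effects, a pooled effect (adjusting for interbody fusion) will be reported". If the effects are not homogeneous, the two analyses are reported separately. For outcome measures in general, "Differences in outcome measures between the 2 pairs of groups, together with 95% confidence intervals, will be calculated", and the t-tests for continuous secondary outcomes follow the same two pairs. Both pairs have ACDP on one side.

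The Sample size section justifies 675 patients by the intention to make two two-group comparisons separately. It assumes annual rates of "2% after arthroplasty and 7% after interbody fusion for the power calculations" and gives no rate for ACD.

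The stated aims are wider than the two pairs. The abstract's Discussion says: "Whether additional interbody fusion or disc prothesis is necessary and cost-effective will be determined by this trial". The opening of Methods/Design sets out to evaluate the prosthesis on one hand, "cervical fusion on the other hand, and compare this to discectomy without any implant". The Background and the main Discussion repeat this. The primary question in Methods/Design, however, concerns only ACDP against each of the other two arms.

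**The concern.** There are three linked problems.

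1. **The reported effect depends on the data.** Whether the reader gets two hazard ratios or one average depends on a check that the trial was not sized for. A non-significant check is then treated as if ACD and ACDF were equivalent controls.
2. **The pooled quantity is ambiguous.** Adjustment for interbody fusion can mean different things when fusion is allocated in one arm only. Under one common coding, the result labelled pooled would be ACDP versus ACD alone.
3. **A promised answer has no named contrast.** Whether a cage adds anything over plain discectomy is a stated aim, yet no estimate or confidence interval for ACDF versus ACD is named.

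At stake is the clarity of the main effect estimate, and whether the trial delivers one of the answers it announces.

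**Working it through.** **The plan's own figures.** With constant hazards, HR = ln(0.98)/ln(0.93) = 0.278, which agrees with the stated 0.28. Sample size: 1.5 × 450 = 675, and 675/0.90 = 750. Both reproduce. A two-group size of 450 means 225 per arm. The sample size is not at fault here.

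**What the homogeneity check tests.** Write the log hazards as a (ACD), f (ACDF) and p (ACDP). Then (p − a) − (p − f) = f − a. The ACDP arm cancels, so homogeneity of the two effects is the same hypothesis as ACDF = ACD.

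**How often the check would pass.** From the article: ACDF 7%, ACDP 2%, three-year accrual, 4.2 years as the last analysis time under H1, and five-year follow-up. Assumed, because the article does not give them: the ACD rate (3% to 5% shown), a two-sided 5% check, uniform accrual and no loss.

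- Hazard: λ = −ln(1 − annual rate).
- Expected events per arm at calendar time T = 4.2: 225 × {1 − [exp(−λ(T − 3)) − exp(−λT)]/(3λ)}.
- Expected events per arm with five years for everyone: 225 × [1 − exp(−5λ)].
- SE of the ACDF-versus-ACD log hazard ratio: √(1/events in ACDF + 1/events in ACD).
- Probability of passing ≈ Φ(1.96 − δ/SE), where δ is the true log hazard ratio.

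Example with ACD at 4% and T = 4.2: the events are 39.7 (ACDF) and 23.4 (ACD). δ = ln(0.0726/0.0408) = 0.575, SE = 0.261 and δ/SE = 2.21. P(pass) ≈ Φ(−0.25) = 0.40.

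| Assumed ACD rate | Events ACDF / ACD, 4.2 y | P(pass), 4.2 y | Events ACDF / ACD, 5 y | P(pass), 5 y |
|---|---|---|---|---|
| 3% | 39.7 / 17.7 | 14% | 68.5 / 31.8 | 2% |
| 4% | 39.7 / 23.4 | 40% | 68.5 / 41.5 | 17% |
| 5% | 39.7 / 28.9 | 71% | 68.5 / 50.9 | 53% |

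Simulation of exponential event times gives 39% and 15% for ACD 4%, and 71% and 53% for ACD 5%.

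**What is then reported.** With ACD at 4%, the true hazard ratios are 0.0202/0.0408 = 0.495 (about 0.50) against ACD and 0.28 against ACDF. In trials that pass the check, the median pooled hazard ratio is about 0.36. Over the whole rule (pooled if the check passes, separate otherwise), nominal 95% intervals cover the individual hazard ratios in about 91–93% of trials. Within the trials that pass at 4.2 years, the figure is about 84–88%, depending on how the pooling is done.

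**What adjustment for fusion does.** The three arms have three log hazards.

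- With a prosthesis indicator and an ordinary 0/1 fusion indicator the model is saturated, and the prosthesis coefficient is p − a, ACDP versus ACD alone. At the rates above it estimates 0.495.
- With centred coding (ACD −0.5, ACDF +0.5, ACDP 0) the coefficient is p − (a + f)/2, the average of the two log hazard ratios. At the same rates it estimates √(0.495 × 0.278) = 0.37.

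The wording allows either.

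**Could the missing contrast inform?** Its power is one minus the pass probability: about 60% at 4.2 years and 83% at five years if ACD is 4%, and 29% and 47% if ACD is 5%.

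**The case against.** The two likelihood ratio tests are planned without condition. ACDF versus ACDP is the main comparison, with its own group sequential analysis, and differences with confidence intervals for both pairs are to be calculated. So pooling affects the presentation of the effect and does not replace the primary tests. This stands, and it limits the point.

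A reader might infer that the adjusted effect does not pool at all. The article does not support that. It fixes neither model nor coding, and centred coding does give a pooled effect. The wording is ambiguous, no more.

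A reader might also take the conditional coverage of 84–88% as the error of the plan. That figure covers only trials passing the check and scores an average against two separate targets. Over the whole rule the shortfall from 95% is small.

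Large differences would mostly be caught: with ACD at 3% the check fails in about 86% of trials at 4.2 years and 98% at five years. The pass rates also rest on an ACD rate and a check level that the article does not give. The homogeneity criterion may be set in the full protocol or analysis plan, so its absence is not counted.

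Finally, the homogeneity check is implicitly the fusion comparison, and the repeated-measures analysis of variance may include all three arms. But a check used only to choose a report is not a reported estimate. The analysis of variance covers only continuous secondary scales and names no fusion contrast.

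**Conclusion.** The point holds as a should-fix. The reporting rule makes separate hazard ratios conditional on a comparison for which the article states no power and no ACD rate. It also sits badly with a sample size justified by two separate comparisons. If ACD is 4% or 5% a year, between about 15% and 71% of trials would be summarised by one pooled figure, depending on the rate and the follow-up. With ACD at 4%, that figure of about 0.36 stands for 0.50 and 0.28. The loss of coverage is modest, at about 91–93% over the whole rule. These sizes rest on the assumed ACD rate, a 5% check, constant hazards and no loss.

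The missing ACDF-versus-ACD contrast is a mismatch between stated aims and named analyses and needs no assumption. It concerns a broader aim, not the primary question. It would be too strong to infer that the primary result is invalid or that a fusion effect would generally be hidden. The primary tests stand, and large fusion effects would usually fail the check.

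**What to change.** In Data Analysis:

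1. Report the hazard ratios for ACDP versus ACDF and ACDP versus ACD, each with a 95% confidence interval, whatever the homogeneity result.
2. Add ACDF versus ACD as a prespecified secondary contrast with a 95% confidence interval, for the primary event and the secondary outcomes. A non-significant result should not be described as equality.
3. If a pooled summary is kept, define it as a fixed-weight average of the two log hazard ratios, with a variance that allows for the shared ACDP arm, and label it descriptive. Replace the phrase about adjusting for fusion with that definition.

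The cost is analysis wording and one further contrast from data already collected; the sample size does not change. The sponsor gives up a possible pooled headline. The added contrast may be imprecise if ACD and ACDF differ little, and the confidence interval will show this.

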### Randomisation procedure

Patients will be randomly allocated to ACD, ACDF, or ACDP. Randomisation will take place on the operating room within 6 weeks after the first visit to the research nurse. A randomisation list is prepared for every participating hospital-nurse combination. Variable sized blocks of random numbers are formed to ensure equal distribution of the randomisation treatments over hospitals and research nurses. The data manager, who is not involved in the selection and allocation of patients, will prepare coded, sealed envelopes containing the treatment allocation. In the operating room, after induction of anaesthesia, the surgeon will open the envelope and the allocated treatment will be performed. Patients and research nurses will be kept blinded for the allocated treatment for 2 years.

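### The t-tests named for the continuous secondary outcomes, including NDI, cannot deliver the baseline adjustment that the same section promises

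*Protocol article*

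**What the plan says.** Three statements in the Data Analysis section of the protocol article bear on the continuous secondary outcomes.

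- On adjustment, with no exception named: "Baseline measurements will be used as covariates in the analyses to increase power".
- On the between-group comparison: "The secondary outcome continuous measures will be compared using two t-tests in the same way". The fallback is given as "or non-parametric counterparts in case of non-symmetrical or distributions with outliers", and transformation of skewed data is also allowed.
- On the course over time: "repeated measurements analyses of variance for the secondary outcome measures (the continuous outcome scales) will also be performed".

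The primary outcome is handled separately: "The primary research objective will be tested using two likelihood ratio tests for the hazard ratio's".

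Table 2 schedules NDI at the research nurse's intake and at ten follow-ups from 2 to 260 weeks. McGill, VAS, SF-36, HADS, Karasek and EuroQol also have an intake measurement. The baseline scores needed for adjustment will therefore exist.

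**The concern.** A t-test compares two means, and its rank counterpart compares two distributions. As ordinarily understood, neither has a place for a baseline covariate. The section thus gives one general instruction (adjust, to gain power) and one specific instruction (use a test that cannot adjust) for the same outcomes. An analyst could report an unadjusted or an adjusted NDI difference and cite the protocol for either.

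NDI is the outcome that the Methods/Design section names as secondary, and the Background links it to the hypothesis in favour of the prosthesis. At stake are the width of its confidence intervals and the power of its comparisons, and the same holds for the pain, quality-of-life and other continuous scales. If the specific sentence prevails, the plan gives up the gain that it states as its reason for adjusting.

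**Working it through.** **1. The plan's own figures.** Two arms accrue 150 × 3 = 450 patients, which is 450/2 = 225 per arm. Three arms need 1.5 × 450 = 675, and 675/(1 − 0.10) = 750. The hazard ratio is ln(0.98)/ln(0.93) = 0.278, stated as 0.28. All of these reproduce. They belong to the primary time-to-event outcome. No SD, target difference or power is stated for NDI or any other secondary outcome, so the check below is in SD units.

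**2. Reference effect for the unadjusted t-test.** Inputs are n = 225 per arm, significance level 0.05 (taken as two-sided; the article does not say) and the normal approximation. The effect with 90% power is

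d = (1.960 + 1.282) × √(2/225) = 0.306 SD.

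**3. Effect of baseline adjustment.** With correlation r between baseline and outcome, adjustment multiplies the residual variance by 1 − r². Then

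power = Φ( d / [√(2/225) × √(1 − r²)] − 1.960 ).

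The detectable effect at 90% power is 0.306 × √(1 − r²), and the number per arm that matches the t-test is 225 × (1 − r²). The article gives no r; 0.3 to 0.7 is an assumed range.

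| r (assumed) | 1 − r² | Power at 0.306 SD | Detectable effect at 90% power | Patients per arm matching the t-test's 225 |
|---|---|---|---|---|
| 0 (t-test) | 1.00 | 90.0% | 0.306 SD | 225 |
| 0.3 | 0.91 | 92.5% | 0.292 SD | 205 |
| 0.5 | 0.75 | 96.3% | 0.265 SD | 169 |
| 0.7 | 0.51 | 99.5% | 0.218 SD | 115 |

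The t-test forgoes 2.5 to 9.5 percentage points of power at that effect. At a smaller effect, where the t-test has 80% power (0.264 SD), adjusted power is 83.6%, 89.9% or 97.5%, a difference of 3.6 to 17.5 points.

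**4. Hospital as a further covariate.** If hospital or nurse explains a share ICC of the outcome variance, adjustment multiplies the variance by 1 − ICC. At 0.306 SD, power rises from 90% to 90.3%, 91.4% or 92.7% for an assumed ICC of 0.01, 0.05 or 0.10. The gain is small.

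**5. Repeated-measures analysis, conditional on its form.** If a classical ANOVA restricted to complete cases were used over the 11 NDI occasions (intake plus ten follow-ups), the share of patients kept would be (1 − m)^11. With independent missingness m of 1%, 2% or 5% per occasion (assumed), that is 90%, 80% or 57%. Missed questionnaires tend to cluster within patients, so independence overstates this loss.

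**The case against.** The best defence is that the general sentence governs: baseline measurements enter all analyses, and the t-test is shorthand for testing an adjusted contrast. That reading is possible for the t-test, but the rank-test fallback makes it strained. It is also fair that the unadjusted t-test stays valid in a randomised trial, that these are secondary outcomes, and that the size of the loss rests on an assumed correlation. Those points stand and limit the weight of the finding; they do not remove the inconsistency. Nor does condensation into an article explain it, since the article prints both instructions.

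Three stronger readings are tempting, and the document does not support them.

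- *Repeated-measures ANOVA also contradicts the adjustment, or breaches intention to treat by losing patients.* This analysis can carry a baseline covariate. The article states no rule that drops patients with a missed visit, does not fix the form of the model, and presents the ANOVA as an addition to the between-group comparison. The loss in step 5 is only a risk of one possible implementation.
- *No analysis uses the randomisation strata, contrary to the covariate promise.* The article does say "A randomisation list is prepared for every participating hospital-nurse combination", and the Data Analysis section mentions neither hospital nor nurse. But the promise concerns baseline measurements, not design factors. Silence on strata in a condensed article is not exclusion, and a likelihood ratio test can be stratified. Leaving the strata out tends to make a test conservative, and the expected cost is small (step 4).
- *Treatment differs by hospital, so hospital must be modelled.* The Intervention section ties the choice of cage to the surgeon's preference and usual practice. Only the length of admission is tied to the hospital.

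**Conclusion.** The inconsistency is real and narrow: the named t-tests and rank tests cannot provide the baseline adjustment promised in the same section. If they are used, the comparisons of NDI and the other continuous secondary outcomes are less precise than they need be, but not biased. The cost is about 2.5, 6.3 or 9.5 points of power at an effect for which the t-test has 90%, for a correlation of 0.3, 0.5 or 0.7. These figures assume that correlation range, 225 patients per arm with data, a two-sided 0.05 level and a normal approximation. Nothing here touches the primary hazard-ratio test, the 45 events or the 750 patients. It is a worthwhile improvement at almost no cost, not a threat to the trial's main conclusion.

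**What to change.** Replace the t-test sentence with a baseline-adjusted comparison for each of the two pairs of arms (prosthesis against discectomy alone, prosthesis against fusion), reported with 95% confidence intervals. Either form meets the plan's own promise:

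- ANCOVA of each continuous outcome at 52, 104, 156, 208 and 260 weeks, with arm and the baseline score of that outcome; or
- one linear mixed model per outcome with arm, time, arm by time and baseline score, using all available visits, with contrasts between arms at those weeks.

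The mixed model is preferable because it can also serve as the repeated-measures analysis, which removes the complete-case risk should a classical ANOVA otherwise be used. The provision for skewed outcomes should then apply within the adjusted model, for example through a transformation named in advance, rather than by switching to an unadjusted rank test. Hospital may be added as a covariate; this is optional and the expected gain is small.

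The cost is a change of wording and modest extra programming. No new data, visits or patients are needed.
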